**Methods/Design:**

This randomised, double-blind, placebo-controlled trial will involve 200 participants with CRCP recruited from medical practices, outpatient departments and the community via print and radio media. Participants will be randomly allocated to a physiotherapy or placebo group using concealed allocation stratified by treating physiotherapist. Both groups will receive 10 sessions of individual standardised treatment over 10 weeks from one of 10 project physiotherapists. For the following 12 weeks, the physiotherapy group will continue a home exercise program and the placebo group will receive no treatment. The physiotherapy program will comprise shoulder joint and spinal mobilisation, soft tissue massage, postural taping, and home exercises for scapular control, posture and rotator cuff strengthening. The placebo group will receive inactive ultrasound and gentle application of an inert gel over the shoulder region. Blinded assessment will be conducted at baseline and at 10 weeks and 22 weeks after randomisation. The primary outcome measures are self reported questionnaires including the shoulder pain and disability index (SPADI), average pain on an 11-point numeric rating scale and participant perceived global rating of change. Secondary measures include Medical Outcomes Study 36-item short form (SF-36), Assessment of Quality of Life index, numeric rating scales for shoulder pain and stiffness, participant perceived rating of change for pain, strength and stiffness, and manual muscle testing for shoulder strength using a handheld dynamometer. To evaluate cost-effectiveness, participants will record the use of all health-related treatments in a log-book returned to the assessor monthly. To test the effect of the intervention using an intention-to-treat analysis, linear regression modelling will be applied adjusting for baseline outcome values and other demographic characteristics. Participant measures of perceived change will be compared between groups by calculating the relative risks and their 95% confidence intervals at each time point using log binomial regression.

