## Methods/Design

### Design

This will be a randomised placebo controlled trial with blinded participants and outcome assessors (Figure 1). The trial comprises a 10-week intervention and a 12-week follow-up (Figure 1). Participants will be assessed immediately before treatment (baseline), immediately after treatment (final) and at 22 weeks (follow-up) post randomisation. The assessments will be performed by the same assessor who will be blind to group allocation.

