### Blinding

To maintain blinding, the plain language statement and consent procedures will inform participants that they have an equal chance of receiving real or placebo physiotherapy but will not disclose details of the actual treatments. A blinded examiner will perform all outcome assessments. Participant blinding will be optimised by using a realistic placebo intervention and by ensuring participants do not attend for treatments or assessments concurrently. Participants will also be requested to refrain from discussing their treatment with the outcome assessor. At trial completion, participants will nominate which group they believed they have been allocated to. The data manager and statistician will be unaware of treatment allocation until completion of analyses.

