Isometric shoulder strength for shoulder abduction, internal and external rotation will be measured using the Nicholas Manual Muscle tester (Lafayette, USA). For shoulder abduction, participants will be positioned in supine with the shoulder in 90 degrees of abduction and the elbow flexed to 90 degrees. The dynamometer will be positioned on the lateral surface of the distal humerus, proximal to the lateral epicondyle. Measurements of external and internal rotation will be performed in sitting with the arm by the side against a folded towel, the elbow flexed to 90 degrees and the forearm in midprone. The dynamometer will be positioned on the distal forearm. One warm up trial followed by three maximal contractions will be performed and the median reading taken. We previously measured 12 people with CRCP on two occasions three days apart. Intraclass correlation coefficient (ICC 2,3) values were 0.95 for abduction, 0.96 for internal rotation and 0.93 for external rotation indicating that test retest reliability was excellent.

A number of other measures will be obtained (Table 3). Participant compliance will be obtained by recording the number of physiotherapy sessions attended (out of a maximum number of 10). Those in the physiotherapy group will complete a daily log-book to record the number of home exercise sessions completed. Adverse events and the use of co-intervention will be recorded in a log-book and by open-probe questioning by the assessor at trial completion. Log-books will be posted back to the assessor on a monthly basis and checked for completion. At the final and followup measurement time points, study participants will be asked to indicate which treatment they believe they have received and reasons for that choice to assess the success of blinding.

Information on direct health care costs, direct non-health care costs and production losses over the 22 weeks will be collected by a logbook posted back to the assessor on a monthly basis and checked for completion. Direct health care costs will include costs of physiotherapy attendance (assumed zero in the placebo group), additional health provider visits, tests, prescription and over the counter medication, professional home care and hospitalisation. These will be valued using published prices for medical costs. Direct non-health care resources will include use of paid and unpaid help, lost time and travel, and number of lost days at work.

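### The protocol gives two schedules for the allocation guess, and the one that asks for reasons at week 10 could disclose the arm to the single blinded assessor before the week-22 assessments

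*Protocol article*

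**What the plan says.** Two sections of the protocol article describe when participants are asked to guess their group.

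- **Blinding:** "At trial completion, participants will nominate which group they believed they have been allocated to". One time point is named, and reasons are not mentioned.
- **Outcome assessment**, in the text after Table 3: "At the final and followup measurement time points, study participants will be asked to indicate which treatment they believe they have received and reasons". Two time points are named, with reasons at each.

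The Design section fixes the terms. Assessments after baseline take place "immediately after treatment (final) and at 22 weeks (follow-up) post randomisation", and "The trial comprises a 10-week intervention and a 12-week follow-up".

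Two further statements bear on assessor blinding. The Design section says "The assessments will be performed by the same assessor who will be blind to group allocation", and the Blinding section says "Participants will also be requested to refrain from discussing their treatment with the outcome assessor".

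**The concern.** The first problem is plain inconsistency: one section implies a single guess at the end of the trial, and the other implies two guesses, the first of them halfway through the assessment schedule.

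The second problem is what the earlier question asks for. A bare guess says what the participant believes and may be wrong. A reason describes what was done to the participant. Here that description can identify the arm, because the two treatments share almost no content. If the reasons reach the assessor at week 10, the person who tests strength at week 22 may by then know the allocation. The plan would also be asking participants to tell the assessor what the Blinding section asks them not to discuss.

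At stake is the blinding of the week-22 assessments, chiefly the hand-held dynamometry, where the tester has a direct part in the measurement.

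**Working it through.** No sample size, power or error-rate figure is involved. The check sets the sections side by side.

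**1. Timing.** The Design section gives 10 weeks of intervention and 12 weeks of follow-up, and 10 + 12 = 22. Trial completion for a participant is therefore week 22, the same visit as follow-up. The final visit is the end of treatment, week 10.

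| Section | Guess at week 10 | Guess at week 22 | Reasons asked for |
|---|---|---|---|
| Blinding | not mentioned | yes | not mentioned |
| Outcome assessment | yes | yes | yes, both times |

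The first guess in the Outcome assessment section thus comes 22 − 10 = 12 weeks before the last set of outcomes. The two terms are unlikely to be loose synonyms. The same paragraph uses trial completion for the questioning on adverse events and co-interventions, and the named visits for the guess.

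**2. What a reason would disclose.** The physiotherapy arm receives massage, joint and spinal mobilisation, taping and exercises (Physiotherapy intervention group, Table 1). The placebo arm receives sham ultrasound and an inert gel, with no exercise instruction and no manual therapy (Placebo group). A participant who mentions exercises or tape, or a machine and gel, has in effect named the arm.

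**3. Who could learn it.** One assessor performs all assessments and must stay blind. The article names the assessor for the adverse-event questioning and names nobody for the guess. Disclosure therefore depends on an unstated fact: whether the assessor hears or reads the answer.

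**4. Which outcomes are exposed.** Week-10 outcomes are affected only if the question comes before them within the visit, and the order is not stated. At week 22, the outcome most open to an unblinded assessor is isometric strength, which Table 3 lists as secondary. For the three primary outcomes the Abstract says "The primary outcome measures are self reported questionnaires", so the assessor's knowledge has a less direct route to them.

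**5. Other routes.** The Outcome assessment section also has log-books posted to the assessor each month, and participants in the physiotherapy arm record home exercise sessions in a log-book. If the exercise entries are among the pages the assessor checks, the arm could become known before week 10, whatever is done about the guess.

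**The case against.** The strongest reply has four parts.

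- **The mismatch may be editorial.** A reader might infer that the Blinding section restricts the question to week 22. It does not: it names trial completion without ruling out an earlier question, and the Outcome assessment section may simply be the fuller statement. This stands as far as it goes. The sections still differ and need aligning, but the difference is one of wording and not a flat prohibition breached.

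- **Assessor unblinding is not stated.** A reader might infer that the plan has the assessor take the reasons. The document does not say so, and a condensed article commonly leaves the handling of forms to the full protocol. This also stands, and it makes the disclosure risk conditional. It does not remove the point, because asking for reasons at week 10 is itself a stated procedure.

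- **Participant bias at week 22 is speculative.** A reader might infer that committing to a belief at week 10 biases the self-rated primary outcomes 12 weeks later. Participants are already told at consent that "they have an equal chance of receiving real or placebo physiotherapy", so the question tells them nothing new about their arm. Their experience diverges after week 10 in any case, since one arm continues home exercise and the other receives nothing. A guess at the end of treatment is also defensible, because it records belief before 12 more weeks of symptom change. The documents support no more than a possibility here.

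- **The blinding index.** A reader might infer that the index in the Data analysis section is deficient because its time point is not given. That is a detail a statistical analysis plan commonly settles, and it could be computed at each visit. It is not part of this point.

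**Conclusion.** The point holds in a limited form. The Blinding and Outcome assessment sections give different schedules for the allocation guess and must be reconciled. Asking for reasons at week 10 creates an avoidable route by which the single assessor could learn allocation before week 22, at odds with the request not to discuss treatment with that assessor.

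The size is small to moderate and cannot be calculated from the document. The conclusion rests on two assumptions: that the assessor might see or hear the reasons, which the article neither states nor excludes, and that participants describe their treatment truthfully. If both hold, the main exposure is week-22 dynamometry, a secondary outcome. The week-10 SPADI comparison on which the sample size is based is untouched unless the question precedes the outcome measures at that visit. The document does not support a claim that the week-22 primary outcomes will be biased. This is an inexpensive improvement to a stated procedure and does not threaten the trial's main result.

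**What to change.** 1. Make the Blinding and Outcome assessment sections give the same schedule.
2. If a week-10 guess is kept, take the guess alone, without reasons. Use a self-completed form filled in after all outcome measures at that visit, sealed and withheld from the assessor. The independent administrator described under Randomisation and allocation could receive it.
3. Ask for reasons only at week 22, after the last outcome has been recorded, by the same sealed route.
4. Protect the monthly log-books in the same way, so that entries on home exercise do not reach the assessor. Without this step the change to the guess form is only partly effective.

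The cost is one form, a sentence in each of the two sections, and a different recipient for the log-books. The information given up is the set of reasons at week 10. Keeping the week-10 guess means that participants still commit to a belief before week 22, so the change protects the assessor's blinding and does not alter any effect on participants' own ratings.

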### Sample size

Sample size was calculated based upon the ability to detect a 10-point difference in improvement in SPADI score, previously reported to indicate a clinically important improvement (or worsening) of shoulder function [41]. Applying power calculations appropriate for analysis of covariance (adjusting for baseline SPADI score), to detect a difference in 10 week SPADI of 10 units assuming a common between-participant standard deviation of 27 and a baseline to 10 week correlation in SPADI scores of 0.45 (from our pilot study), 91 participants per group will be required to achieve 80% power at a two-sided 5% significance level. Including the 10 week and further 22 week follow-ups in a repeated measures analysis increases the power to 85% assuming a conservative correlation of 0.8 between all post-baseline measurements and a uniform physiotherapy effect. We will allow for a 10% loss to follow-up and aim to recruit 100 participants per group.

### Data analysis

All analyses will be conducted on an intention-to-treat principle using all randomized participants. Missing data will be replaced by the last score carried forward. Demographic characteristics and baseline data will be summarised by descriptive statistics. An index will be computed to assess the success of blinding [47]. This index takes the value one for complete blinding and zero for complete lack of blinding.

For outcomes measured using an essentially continuous scale, differences in mean change from baseline to each time point will be compared between groups using linear regression modelling adjusting for baseline levels of the outcome measure. Model assumptions will be checked by standard diagnostic plots [48]. For analysis across all time points simultaneously, accounting for repeated measurements, we will estimate the differences between groups using generalised estimating equation models for the post-baseline measurements with adjustment for baseline measurements, a robust variance and unstructured working correlation [49]. Constancy of the difference between groups over time will be assessed by fitting models which include a term for the interaction between treatment and time. Sensitivity analyses include repetition of analyses with calculation of bootstrap standard errors, and identification of influential individuals by sequentially omitting each participant and refitting the model.

Participant measures of perceived improvement following physiotherapy or placebo treatments will be compared by calculating the relative risks and their 95% confidence intervals at each time point using log binomial regression [50]. Repeated measures relative risk calculations will be performed using generalised estimating equations with a logarithmic link function, robust variance and unstructured correlation [49]. As above, models including a term for the interaction between treatment and time will be fit to assess the constancy of the difference between groups over time.

The primary economic evaluation will take the form of a cost effectiveness study with a range of outcome measures including the incremental cost per extra person with a clinically significant improvement in pain, per extra person perceived to be recovered, and per extra quality adjusted life years (using the AQoL over 22 weeks). A social perspective on costs will be taken that includes resource use incurred both by health services and by the participant irrespective of the source of payment. The inclusion of time/productivity gains is controversial and the cost effectiveness ratios will be calculated with and without these indirect costs. All health care costs will be included, however to reduce the impact of extreme values, if inpatient hospital costs are unrelated to CRCP they will be excluded. Standard methods of economic evaluation alongside a clinical trial [51] will be used to evaluate the differences in resource use and health outcomes over 12 months between groups. The statistical analysis of costs data will be similar to outcome data although adjustments for overdispersion may be necessary. Confidence intervals for incremental cost effectiveness will be calculated directly using non-parametric bootstrapping [52]. In addition we will calculate a cost effectiveness acceptability curve based for a range of hypothetical money values of outcomes [53]. This will be done using individual cost and outcome data over the 22 weeks or, if adjustments for imbalance at baseline are necessary, using regression analysis [54]. Hypothetical money values will be taken from the decision making literature but the trial will also ask patients in each arm of the trial their willingness to pay for the treatment prior to and after treatment. This will not only provide money values for the calculation of net benefits but also provide evidence on the influence of health experience on the value of health outcome to patients.

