**Other measures**	

Compliance	• Number of therapy visits • Physiotherapy group: Completion of home exercises via log-book
Adverse effects	Log-book and open probe questionning

Average pain, worst pain and pain on three self-selected activities (over the past week) will be measured by separate 11-point numeric rating scales [12] numbered in 1 cm intervals. The amount of weakness, stiffness and interference with activities of daily living (over the past week) will be measured similarly.

Participant perceived global rating of change overall and in pain, strength, and stiffness (since commencement) will be recorded on separate 5 point Likert scales (1-much worse, 2-slightly worse, 3-no change, 4-slightly better, 5-much better). Measuring participant perceived improvement using a rating of change scale has been shown to be a clinically relevant and stable concept for interpreting truly meaningful improvements from the individual perspective [42]. A successful outcome will be defined a priori as 'much better' on the rating scale.

Health-related quality of life will be measured using the Medical Outcomes Study 36-item short form (SF-36) (8 subscales scaled from 0–100 where a higher score represents better health) [43]. This the most widely used generic measure of health related quality of life and permits comparison of the impact of disease and treatment across studies and populations. The clinimetric properties of the SF-36 have been well established on samples from diverse populations [43,44]. We will also use the Assessment of Quality of Life (AQoL) instrument. The AQoL comprises 15 items on ordinal scales with four levels per item covering five dimensions (illness, independent living, social relationships, physical senses and psychological wellbeing). It produces a single utility index that ranges from -0.04 (worst possible health-related quality of life) to 1.00 (full health-related quality of life). The AQoL has strong psychometric properties [45,46]. The AQoL can also be converted into a utility index to calculate quality adjusted life years (QALY).

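### Last score carried forward, the only stated missing-data rule, can bias the SPADI comparison when loss falls before week 10 and leaves a missing week-10 global rating undefined

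*Protocol article*

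**What the plan says.** Under Data analysis, the protocol article sets the analysis population and the missing-data rule in consecutive sentences: "All analyses will be conducted on an intention-to-treat principle using all randomized participants", then "Missing data will be replaced by the last score carried forward". The rule is not limited to any outcome or visit. The Design section gives three assessments: baseline, 10 weeks and 22 weeks.

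Table 3 lists three primary outcomes: SPADI, average pain over the past week, and the overall global rating of change. Outcome assessment describes the last of these as a rating of change from the start of the trial: "Participant perceived global rating of change overall and in pain, strength, and stiffness (since commencement) will be recorded on separate 5 point Likert scales". Success is the top category of that scale, and the arms are compared by relative risk at each time point.

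The Sample size section plans "to detect a difference in 10 week SPADI of 10 units". With an SD of 27 and a correlation of 0.45 between the baseline and week-10 scores, it arrives at 91 per group for 80% power. On attrition it says: "We will allow for a 10% loss to follow-up and aim to recruit 100 participants per group".

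**The concern.** With two post-baseline visits, the last score for anyone lost before week 10 is the baseline score. Carrying it forward records no change at week 10 and again at week 22. The placebo is designed to reproduce therapist contact and belief in treatment (Placebo group section), so some improvement is to be expected in both arms. Zero change is then a poor guess for either arm, and it stays poor even if participants are lost purely at random.

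Two things are at stake. First, the SPADI and pain contrasts come to depend on how many participants leave each arm before week 10. Unequal loss is plausible, because only the physiotherapy arm is asked to do home exercises. Second, the global rating is a primary outcome with no baseline value. For a missing week-10 rating the rule supplies nothing, yet the plan promises to analyse everyone randomised. Someone would have to choose a value later, on a primary outcome.

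**Working it through.** **Inputs from the Sample size section.** Effect δ = 10, SD 27, baseline to week-10 correlation 0.45, two-sided 5%, 100 recruited per arm, 10% loss. **Assumed, because the protocol does not give them:** mean placebo improvement m (0, 10 or 20 points), the timing of loss, any imbalance in loss, and loss unrelated to the score within each arm.

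**1. The plan's own figures.** Residual SD after baseline adjustment = 27 × √(1 − 0.45²) = 24.11. Then n = 2 × (1.960 + 0.842)² × 24.11² / 10² ≈ 91.3, so 91 or 92 per group; power with 91 is 79.9%. For repeated measures, the SD is 27 × √((1 + 0.8)/2 − 0.45²) = 22.55, and power with 91 is 84.9%, against 85% stated. Allowing for loss, 91 / 0.9 = 101.1, against 100 stated. The section reproduces to within rounding.

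**2. What carry-forward does to the mean.** Let p1 and p0 be the proportions lost before week 10 in the physiotherapy and placebo arms. The recorded mean improvements are (1 − p1)(m + δ) and (1 − p0)m, so the expected estimate is

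(1 − p1)δ + (p0 − p1)m.

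**3. Equal early loss, p1 = p0 = 0.10.** The estimate is 0.9 × 10 = 9.0 for every m. The pooled residual variance is 0.9 × 24.11² + 0.09 × [(1 − 0.45)² × 27² + A], where A is the average over the arms of the squared mean improvement: A = 50, 250 or 650 for m = 0, 10 or 20. The SDs are 23.4, 23.8 and 24.5. With 100 analysed per arm, power = Φ(9.0 / (SD × √(2/100)) − 1.96).

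| Assumed m | Estimate | Power, formula | Power, simulated |
|---|---|---|---|
| 0 | 9.0 | 78% | 76% |
| 10 | 9.0 | 76% | 76% |
| 20 | 9.0 | 74% | 73% |

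The last column is from 10,000 simulated trials per row (simulation standard error about 0.4 points). Allowing for that error, the range is about 72% to 78%. Analysing only the 90 expected per arm with observed data gives 79.5% by formula and 78% to 79% in the same simulations.

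**4. Timing.** If 5% are lost before week 10 and 5% after, the estimate is about 9.5 and week-10 power is 79% to 81%. If all loss falls after week 10 and the effect is uniform, the estimate stays at about 10 and power is about 83%. For the repeated-measures analysis with all 10% lost early, power is 79% to 83%, against 84.5% with 90 observed per arm.

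**5. Unequal early loss.**

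- Physiotherapy 15%, placebo 5%, true effect 10: 8.5 − 0.10 × m = 8.5, 7.5 or 6.5 for m = 0, 10 or 20. Simulated power is about 73%, 60% or 46%.
- Physiotherapy 5%, placebo 15%, no true effect: 0.10 × m = 1.0 or 2.0 points of spurious benefit for m = 10 or 20. Simulated type I error is about 6% or 9%. At m = 0 there is no bias.

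**6. Global rating.**

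| Pattern of missing ratings | Earlier rating to carry |
|---|---|
| Week 22 only | Week-10 rating |
| Week 10 only | None |
| Both visits | None |

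In the last two rows the rule and the promise to analyse all randomised participants cannot both be kept.

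**The case against.** The strongest reply is that the effect is small at the loss the plan expects, and that the larger figures come from assumptions. Much of this stands. The protocol gives neither the timing of the 10% loss, nor any imbalance, nor the placebo improvement. The 46% power and 9% type I error need 15% against 5% loss, all before week 10, together with a 20-point placebo improvement. The simulated loss was random within arm, which makes the observed-data analysis unbiased by construction; the trial cannot guarantee that.

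A reader might infer four stronger points, and the protocol does not support them.

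- *That the rule cannot be applied to the global rating at all.* It can at week 22 when a week-10 rating exists.
- *That the 80% and 85% power statements are wrong.* They reproduce. The shortfall arises in the analysis, and only when enough of the loss is early.
- *That filling in values inflates false positives in itself, or invalidates the GEE.* With equal loss and no true effect, the simulated week-10 type I error was 5.1%. The planned robust variance means that a distorted working correlation costs efficiency, not validity.
- *That missing-data sensitivity analyses or cost and AQoL imputation have been omitted.* The protocol introduces its list with an open verb, "Sensitivity analyses include repetition of analyses with calculation of bootstrap standard errors, and identification of influential individuals by sequentially omitting each participant", and an analysis plan that is not shown may hold the rest.

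What the reply does not remove is that carry-forward is a stated rule, not a detail left open. It enters zero change for early losses and is undefined for part of a primary outcome.

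**Conclusion.** The point holds in a limited form. As the only stated rule, last score carried forward shrinks a true 10-point SPADI effect to about 9.0 when 10% of each arm is lost before week 10. Week-10 power is then about 72% to 78% instead of about 79%, over an assumed placebo improvement of 20 down to 0 points. The loss of power is modest, and it is slight or absent if participants leave later and the effect is uniform.

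The weightier problem is unequal early loss, where the bias can run in either direction and its size depends on quantities that the protocol does not give. Average pain follows the same rule and shares the zero-change entry, but its bias was not computed. For the overall global rating, the gap is confined to a missing week-10 rating and to participants who miss both visits.

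**What to change.** Replace the carry-forward sentence as the primary rule, and do so before allocation is revealed.

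- **Continuous outcomes:** fit a likelihood-based repeated-measures model to all observed post-baseline data, adjusted for baseline; or multiply impute by arm and then run the planned regression and GEE. Either is valid if data are missing at random given what the model includes. Under the first option, a participant with no post-baseline visit adds nothing to the estimate, so the all-randomised sentence should be worded to fit. Under the second, everyone is retained.
- **Overall global rating of change:** multiply impute from arm, SPADI and pain, so that a missing week-10 rating and a participant missing both visits have a defined treatment.
- **Carry-forward:** keep it at most as a labelled sensitivity analysis.

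The sample size need not change on this account. The cost is some rewording, a little more programming, and slightly wider intervals than single imputation would report. No additional data are needed.
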